##### Mindfulness skills

The 37-item Comprehensive Inventory of Mindfulness Experiences (CHIME) is used to measure mindfulness [42]. Items are rated on a 6-point scale ranging from 1 to 6, with higher scores indicating higher levels of mindfulness. The CHIME provides eight subscales: awareness of internal experiences, awareness of external experiences, acting with awareness, accepting and non-judgmental orientation, decentering and non-reactivity, openness to experiences, relativity of thoughts, and insightful understanding. In the present study the total score and scores of the subscales will be used. The CHIME is a valid and reliable measure for use among adults [43, 44].

##### Health-related quality of life

Health-related quality of life will be assessed using the Quality of Life Questionnaire (QLQ-C30) [45]. This is a multidimensional, cancer-specific quality-of-life questionnaire developed by the European Organization for Research and Treatment of Cancer (EORTC) Study Group on Quality of Life for use in international clinical trial settings. It includes five functional scales (physical, role, emotional, social and cognitive functioning), three symptom scales (fatigue, pain, nausea and vomiting) and a global health status/quality of life scale. In this study we will only use the global health status/quality of life scale.

### Neurocognitive tests

Objective cognitive performance is evaluated using a neurocognitive test battery, covering several domains: (1) Attention and concentration (Bourdon-Wiersma Dot Cancellation Test [45, 46], Trail Making Test (TMT) [46–49]); (2) Memory (Auditory Verbal Learning Test (AVLT), parts A and B [46], Weschler Adult Intelligence Scale (WAIS) III forward digit span [50]); (3) executive functioning (Stroop Color Word Test [51, 52], Controlled Oral Word Association Test (COWAT) [46, 53], Trail Making Test (TMT), form B [46–49], WAIS III backward digit span, and WAIS III letter-number sequencing [50]) and (4) cognitive/psychomotor processing speed (WAIS III digit symbol-coding [50], Nine-hole Peg Test (9HPT) [54, 55] and Trail Making Test (TMT), form A [46–49]). Additionally, verbal IQ is estimated by the Dutch Adult Reading Test (DART) [56]. The neuropsychological test battery has high reliability and good validity in our study population [9–11].

### Structural and functional changes in the brain

Non-invasive MRI imaging of the brain (high-resolution, anatomical, T1-weighted imaging, (T1-w imaging) multi-shell diffusion imaging (DWI) and functional MRI (fMRI) will be used to study both structural and functional changes in the brain. All subjects are imaged on a 3-Tesla scanner (Achieva, Philips, Amsterdam, the Netherlands) with a 32-channel phased-array head coil.

#### High-resolution, 3D, T1-weighted image (3D-T1-w, duration ± 5 min)

The 3D-T1-w anatomical image will be acquired using a 3D-turbo field echo (TFE) sequence and is used to assess volumetric changes in the brain and as anatomical reference for both functional and diffusion MRI.

#### Resting-state functional MRI (rs-fMRI, duration ± 7 min)

Whole-brain, T2*-weighted echo planar images (EPIs), sensitive to blood oxygenation level dependent (BOLD) contrast will be used to acquire functional MRI (fMRI) scans during “resting state.” Participants are asked to close their eyes, lie still and not to fall asleep.

#### Active functional MRI (afMRI, duration ± 8 min)

Whole-brain, T2*-weighted EPIs, sensitive to blood oxygenation level dependent (BOLD) contrast will be used to acquire functional MRI (fMRI) scans while participants perform a memory task in the scanner. The fMRI task consists of a visual N-back sequential letter task used to assess working memory brain activation [46, 47]. Four conditions are tested: 0-back, 1-back, 2-back and 3-back in a blocked design. The 0-back control condition has a minimal working-memory load; participants need to decide if the current letter matches a single target letter that was specified before. In the 1-back condition, participants need to asses if the current letter matches the previous letter. During the 2-back (3-back) condition, participants need to assess whether the current letter matches the letter that has been presented 2-back (3-back) in the sequence. Participants practice the task before the scanning session. During the MRI scanning session, participants respond by pressing a button to indicate whether the item matches the target condition.

#### Diffusion-weighted imaging (DWI, duration ± 20-30 min)

Whole-brain, multi-shell diffusion-weighted EPIs will be acquired with low and high b values, ranging from 0 to 4000 and with number of directions ranging from 20 to 60. Diffusion images will be used to assess microscopic white matter microstructural differences.

### Biomarkers of inflammation

Blood samples will be collected from all participants at the three time points, on the same day as completion of the other assessments. Levels of pro-inflammatory cytokines such as interleukin (IL)-1, IL-6, IL-8, tumor necrosis factor (TNF)-α, interferon (IFN)-γ and monocyte chemoattractant protein-1 (MCP-1) and C-reactive protein (CRP) will be determined with bead-based multiplex immunoassays and compared between groups and time points.

### Analysis plan

Primary outcome measures:
The difference in mean change scores from the baseline on the CFQ between groups; andThe difference in mean change scores from the baseline on the connectivity in the attention network between groups.

Secondary outcome measures:
Changes in neurocognitive test scoresChanges in emotional distress, fatigue and mindfulness skillsChanges in brain white and gray matter structureChanges in functional brain activity during N-back taskChanges in functional connectivity during resting state; andChanges in biomarkers of inflammation

### Data analysis

Analyses will be done both per protocol and intention to treat. Analyses are based on general linear modelling and multilevel mixed-effects modelling. The impact of the intervention will be tested (confirmatory) via a multilevel model with two levels (time points nested within persons). Results will be controlled for false discovery rate [48]. Predictors are time (level-1 predictor), condition (level-2 predictor) and cross-level interactions. To evaluate the process of change a mediation analysis will be performed. Mediation will be tested (exploratory) by adding potential mediators (e.g., different mindfulness facets) and their interaction with condition and time in the intervention model. Time practicing will be tested (exploratory) as a potential moderator. Models are based on the procedure described in Bauer et al. (2006) [49].

State of the art image processing techniques will be used to analyze the MRI images and study both structural and functional differences longitudinally within the groups and between the groups. Voxel-based morphometry (VBM) will be used to study structural changes in the brain. Additionally, advanced multi-shell diffusion images will be processed and analyzed using ExploreDTI/Metrics (DTI, fixel-based analysis, CSD tractography), NODDI modelling software and in-house developed software. This will include head-motion and eddy-current correction and will use inverse phase encoding images and B0 maps for optimizing correction procedures. Seed-based analysis, independent component analysis (ICA) and graph theory will be applied to analyze the resting state fMRI data and assess brain connectivity. From the MRI data we will generate maps reflecting grey matter volume, white matter properties (e.g., fractional anisotropy, neurite density index, orientation dispersion index) and brain connectivity. Voxel-based statistical analysis using the general linear model and non-parametric statistics will be used to find significant differences (*p* < 0.05) in imaging parameter maps between time points and groups. Statistical parametric mapping on a voxel-by-voxel basis will be conducted by using a general linear model approach to assess brain activation during the N-back memory task. Contrast images comparing pairs of working-memory load conditions (e.g., 3-back > 0-back) will be created for each patient and will be used in second-level analyses to assess differences between time points and groups (confirmatory tests for H1 and H2, exploratory test for H3).

The association between the obtained outcomes, psychological and behavioral outcomes based on the scores of retrospective questionnaires, neuroimaging parameter maps, the performance on neurocognitive tests and biomarkers of inflammation will be investigated using correlation analysis.

The number of patients in this study (40 patients in each group) is based on: (1) earlier studies that investigated the effects of MBI on the brain in which effects where shown after MBI in groups of *n* = 20 (longitudinal design [50] and *n* = 13 (cross-sectional design) [51, 52]; (2) the one study that already investigated the impact of MBI on cognitive impairment after cancer treatment. This study reported an impact of MBI on cognitive functioning with a design of *n* < 40 in the different study arms [53].

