### Interventions

#### Intervention group – MBI

The MBI adheres to a standardized protocol developed from the MBSR curriculum [33] and the mindfulness-based cognitive therapy for cancer [34]. The program was adjusted for women, who have an active life, combining job activities with (often) motherhood, and consists of four 3-h group sessions spread over 8 weeks. Each session consists of guided experiential mindfulness exercises (e.g., focus on the breath, body scan, breathing space, mindful movement, sitting meditation), sharing of experiences of these exercises, reflection in small groups, psycho-education (e.g., on topics such as stress, fatigue, fear of cancer recurrence, self-care) and review of homework exercises. The program aims to: (1) increase present moment awareness and recognize entanglement with one’s thoughts and emotions; (2) teach acceptance and mindfulness as an alternative strategy for dealing with problematic thoughts and feelings, and how these may be used to facilitate value-based actions. The program is led by two clinical psychologists who are skilled trainers following standardized procedures. In between the group sessions participants are contacted by phone or mail for a short check-up and a kind reminder to continue their daily practice. The training is supported by the use of homework exercises and audio material. Daily home practice will be strongly encouraged.

Attendance to the group sessions will be monitored as well as daily home practice (see further).

The MBI will be delivered by two clinical psychologists with experience in delivering MBIs to breast cancer patients. Treatment fidelity and trainer adherence will be established using randomly selected video-recordings of the sessions that will be analyzed by independent raters. This will be done using the Mindfulness-based Intervention – Teaching Assessment Criteria [35].

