#### Active control group – physical training

This intervention is based on the recommended levels of physical activity for adults aged 18–64 years from the World Health Organization. These recommendations are the same for women after any breast cancer treatment [36]. This program will consist of four 2-h group sessions spread over 8 weeks. Each session will consist of psycho-education (e.g., on topics such as the basics of movement, advantages of physical activity, and training principles), endurance and resistance training, stretching, balance and relaxation exercises, sharing of experiences of these exercises and review of homework exercises.

The goal of the program is: (1) to improve physical functioning, physical fitness, strength, flexibility and balance and (2) to increase knowledge about physical activity. Participants will receive exercise material and homework assignments which they are expected to follow daily. The physical training is led by a physiotherapist experienced in oncology revalidation.

Attendance to the group sessions will be monitored as well as daily home practice.

The specific elements of each session in both programs are described in Table 1.

**Table 1 Tab1:** Content of each session of the mindfulness-based intervention (MBI) and physical training

Program	MBI	Physical training
Session 1	**Discovering that we function on automatic pilot and kind attention to the body** Pause exercise, ground rules, grounding practice, raisin exercise, body scan, sitting meditation 1 (focus on the breath & coming back to it), overview home practices	**Introduction to international physical activity guidelines, responsible training and explanation of the movement diary** Aerobics, strength exercises and stretching. Progressive relaxation. Overview home practices
Session 2	**Kind attention to the body and the breath** Body scan, sitting meditation 2 (focus on the breath and expanding to sensations in the body and the body as a whole), standing in mountain, mindful walking, pleasant experience and entanglement (thoughts – feelings – sensations), 3-min breathing space, “Thought on a thread” practices (feet on the floor, coming to the breath, kind wishes), overview home practices	**Exploring different training principles and the advantages of physical training** Aerobics, Thera-Band strength exercises, stretching. Body scan. Overview home practices

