#### TAU control group – usual care

Participants in the TAU control group will continue to receive their usual care. They will complete assessments at exactly the same time points as the intervention groups, i.e., at baseline (T0), post intervention (T1) and at 3 -months’ follow-up (T2). Upon completion of the final assessment, the control group will be offered the MBI.

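### The confirmatory two-level model has no training-group term although both active arms are delivered in groups; if change is correlated within groups, type I error rises above nominal, more for H2 than for H1

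*Protocol article*

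**What the plan says.** The Data analysis section of the protocol article fixes the confirmatory model. The effect of the intervention is to be "tested (confirmatory) via a multilevel model with two levels (time points nested within persons", and "Predictors are time (level-1 predictor), condition (level-2 predictor) and cross-level interactions". Neither statement includes a term for the training group. The only error control named there is the false discovery rate.

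The intervention sections describe group delivery in both active arms:

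- **MBI:** the program "consists of four 3-h group sessions spread over 8 weeks", with "sharing of experiences of these exercises, reflection in small groups" as part of each session. "The program is led by two clinical psychologists who are skilled trainers following standardized procedures".
- **Physical training:** "This program will consist of four 2-h group sessions spread over 8 weeks", also with shared discussion of the exercises. "The physical training is led by a physiotherapist experienced in oncology revalidation".
- **TAU:** "Participants in the TAU control group will continue to receive their usual care". Its participants are offered the MBI only after their last assessment.

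H1 sets each active arm against TAU, and H2 sets MBI against physical training. The primary CFQ outcome is the between-group difference in mean change from baseline. The same section names second-level imaging analyses, built on one contrast image per patient, as confirmatory for H1 and H2, again with no group term.

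**The concern.** Patients are randomized one by one, but from the first session those in an active arm share a training group: the same peers, the same exchange of experiences and the same course. Peer exchange is a stated ingredient of both programs, so some correlation of change within a group is plausible. Individual randomization does not prevent it, because it arises after allocation.

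A model with only time points within persons treats 40 group-trained patients as 40 independent changes. If the correlation is positive, the standard error of the condition-by-time contrast is too small, and the test leans towards declaring an effect. H2, the claim that MBI beats an active comparator, is the more exposed because both of its arms are clustered.

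This is not a detail left to an analysis plan that is not shown. The article itself states how many levels the confirmatory model has and what they are.

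**Working it through.** **No planned figure to reproduce.** The 40 per arm is justified only by the size of earlier studies. No effect size, SD, power, ICC or group size is given.

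**Inputs**

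- From the article: 40 per arm; both active arms group-delivered; TAU not.
- Assumed: equal training groups of size m = 8 to 12; ICC of change from 0 to 0.10; two-sided nominal 5%. The article states p < 0.05 only for the imaging maps.

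**Formulas**

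- Design effect in a group-delivered arm: DE = 1 + (m − 1) × ICC. In TAU, DE = 1.
- Ratio of true to model standard error: r = √DE for H2, and r = √((DE + 1)/2) for H1.
- Actual type I error = 2 × (1 − Φ(1.96/r)).

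**Worked case, m = 10 and ICC 0.05.** DE = 1 + 9 × 0.05 = 1.45, so 40 patients carry the information of 40/1.45 = 27.6.

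- H2: r = √1.45 = 1.204; 1.96/1.204 = 1.628; error 10.4%.
- H1: r = √(2.45/2) = 1.107; 1.96/1.107 = 1.771; error 7.7%.

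| m | ICC | DE | H2 | H1 |
|---|---|---|---|---|
| any | 0 | 1.00 | 5.0% | 5.0% |
| 8 | 0.01 | 1.07 | 5.8% | 5.4% |
| 8 | 0.05 | 1.35 | 9.2% | 7.1% |
| 10 | 0.05 | 1.45 | 10.4% | 7.7% |
| 10 | 0.10 | 1.90 | 15.5% | 10.4% |
| 12 | 0.10 | 2.10 | 17.6% | 11.5% |

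**Simulation at m = 10, ICC 0.05.** A t-test on change scores (40,000 trials) rejected in 10.6% (H2) and 7.9% (H1). A two-level random-intercept model with three arms and three time points (8,000 trials) rejected in 11.4% and 8.6%. At ICC 0 that model gave 4.9% and 5.0%.

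**Where the group effect must sit.** Baseline precedes randomization, so a training group can affect only the later measurements, that is, the change. A random group intercept adds the same amount to every time point of a patient, so it cancels from post minus baseline. In 300 simulated two-arm trials (4 groups of 10 per arm, ICC of change 0.05), the two-level model and a three-level model with only a random group intercept gave the same mean standard error for the interaction (0.226) and the same rejection rate (10.0%).

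**Power under a correct model.** Take d = 0.63, chosen because 40 independent patients per arm then give 80% power: SE = √(2/40) = 0.224 and 0.63/0.224 = 2.82. With 4 groups of 10 per arm and ICC 0.05, SE = √(2 × 1.45/40) = 0.269 and 0.63/0.269 = 2.34. H2 has about 2 × (4 − 1) = 6 degrees of freedom, so the critical value is 2.447 and power is about 50%. With 6 degrees of freedom and a true ICC of 0, it is about 65%.

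**The case against.** The strongest reply is that the harm depends on a quantity nobody has seen. At ICC 0 there is no inflation, and at ICC 0.01 with groups of 8 it is under one percentage point. The largest figures need both the largest assumed group and the largest assumed ICC. A reader might infer that the type I error does exceed 5%, or that each active arm was run in about four groups. The article supports neither: it gives the number and length of sessions, but not how many patients sit in a group or how strongly their changes correlate. This part of the reply stands, and the point is therefore conditional.

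The reply can add that 5% is not a stated level for the CFQ model and that results pass through false discovery rate control. The percentages above are therefore per-contrast rates, not the error rate of the whole procedure. That is right, but false discovery rate control takes the p-values as valid and cannot mend those built on standard errors that are too small.

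Finally, a group-level variance from few groups is imprecise and costs power, so one could keep the two-level model and report the clustered one as a sensitivity analysis. The cost is real and has to be stated. It does not justify a confirmatory test that rests on zero within-group correlation, when the error would favour a claim of efficacy.

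**Conclusion.** The concern holds in conditional form. The article fixes a confirmatory model without a training-group level for a partially nested design. With any positive within-group correlation of change, the standard errors are too small and the type I error exceeds nominal, by more for H2 than for H1. With groups of 8 to 12, a nominal 5% and ICC from 0 to 0.10, it runs from 5.0% up to 17.6% for H2 and 11.5% for H1. These figures rest on the assumed group sizes, ICC values and level, and they are not estimates for this trial.

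A reader might also infer that a group term would make H2 a clean comparison of programs. It would not: two psychologists deliver one arm and a physiotherapist the other, so trainer remains confounded with arm.

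**What to change.** - Record the training-group ID for every patient in the two active arms. Attendance at sessions is already monitored, but the article does not say that group membership is stored.
- In the Data analysis section, replace the two-level model with a partially nested one in which the training-group random effect acts on change from baseline. Suitable forms are a group-by-post-baseline-time random effect, or a group random effect in a model of change scores or of baseline-adjusted follow-up scores.
- Place that effect in the two active arms only, with TAU patients as singletons. Allow arm-specific residual variance, and use Kenward-Roger or Satterthwaite degrees of freedom.
- State that a random group intercept alone is not sufficient.
- Apply the same group structure to the second-level imaging tests named as confirmatory for H1 and H2.
- Report the estimated ICC, and acknowledge the trainer-by-arm confounding when interpreting H2.

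The change needs one ID variable and revised model wording; patients, programs and visits are untouched. The price is wider intervals and lower power, chiefly for H2, where few groups leave few degrees of freedom. That loss should be stated openly in the plan.

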**Methods/design:**

The present study is a three-arm, parallel-group, randomized controlled trial with assessments at baseline, 1 to 3 weeks after the intervention and at 3 months’ follow-up. One hundred and twenty breast cancer patients who ended treatment a minimum of 6 months and a maximum of 5 years before, and who have cognitive complaints, will be enrolled. They will be randomized into one of the following three study arms: (1) a mindfulness-based intervention group (*n* = 40), (2) an active control condition based on physical training (*n* = 40), or (3) a treatment as usual (TAU) control group (*n* = 40). Both the mindfulness-based intervention and the active control condition consist of four group sessions (3 h for the mindfulness condition and 2 h for the physical training) spread over 8 weeks. The primary outcomes will be cognitive symptoms as measured by the Cognitive Failure Questionnaire and changes in functional brain connectivity in the attention network. Secondary outcomes will be (1) levels of emotional distress, fatigue, mindfulness, quality of life; (2) neurocognitive tests; (3) structural and functional brain changes using MR imaging and (4) measures of inflammation.

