### Design

This is a single-centre RCT with three study arms and stratified random allocation. Participants in the control condition will receive care from the treatment centre as usual and participants in the intervention groups will receive MBI or a physical training as well as their usual care. The intervention format is equivalent in both intervention conditions. Study evaluation will be done by comparing within and between the three groups. The potential effect will be assessed on a series of outcome measures. Measurements will take place at baseline (i.e., 1–3 weeks before randomization), 1–3 weeks after the intervention and 3 months after the intervention. Participants are allowed to withdraw without giving a reason at any time. There will be no follow-up assessments of these participants. The development of the study protocol followed the SPIRIT (Standard Protocol Items: Recommendations for Interventional Trials) guidelines [30]. The planned flow diagram of this trial is presented in Fig. 1. The protocol is reported according to the Standard Protocol Items: Recommendations for Interventional Trials (SPIRIT; Fig. 2 and Additional file 1). This study was approved by the Medical Ethics Committee of UZ/KU Leuven on 9 July 2018 (S59396). This study was registered with ClinicalTrials.gov (NCT03736460) on 8 November 2018.

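### False-discovery-rate control of the confirmatory tests does not hold the chance of a false primary claim at 5%; it can reach about 12–13% if every contrast is tested at every visit

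*Protocol article*

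**What the plan says.** The abstract of the protocol article names two primary outcomes: "The primary outcomes will be cognitive symptoms as measured by the Cognitive Failure Questionnaire and changes in functional brain connectivity in the attention network". The Analysis plan section repeats them as between-group differences in mean change from baseline.

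The Aim and objectives section turns these into pairwise claims. H1 says that MBI and physical training each beat TAU, which is two contrasts. H2 says that MBI beats physical training, which is a third.

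The Design section places the post-baseline measurements "1–3 weeks after the intervention and 3 months after the intervention". Neither visit is singled out as primary.

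The Data analysis section gives these tests confirmatory status, "The impact of the intervention will be tested (confirmatory) via a multilevel model with two levels", and states the multiplicity rule: "Results will be controlled for false discovery rate [48". It gives no error level for that rule. The only threshold in the section belongs to the voxel-based analyses, which "will be used to find significant differences (*p* < 0.05) in imaging parameter maps between time points and groups".

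**The concern.** A test called confirmatory normally carries a guarantee: if the treatment does nothing on a given primary hypothesis, the chance of claiming otherwise anywhere among the primaries is at most 5%. False-discovery-rate control gives that guarantee only when every hypothesis in the family is null. Once some effects are real and are rejected, the cut-off for the remaining hypotheses relaxes.

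This matters in the situation the investigators expect. Suppose MBI clearly improves CFQ scores relative to TAU. That success makes it easier to declare a connectivity effect, or a superiority of MBI over physical training, that does not exist. Those are the two claims on which the mechanism and the specificity of MBI would rest.

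**Working it through.** The article states no family-wise error, so there is no figure of its own to reproduce.

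**Inputs from the article.** Two primary outcomes (abstract; Analysis plan), three contrasts (H1 and H2), two post-baseline visits (Design) and 40 patients per arm (abstract; Data analysis).

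**Assumptions.** False discovery rate at 5% by the Benjamini-Hochberg (BH) step-up rule; two-sided tests; correlation 0.6 between visits and 0.2 between outcomes; the effect sizes below, in SD units.

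**Step 1, count.** If each contrast is tested at each visit: 2 × 3 × 2 = 12 tests.

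**Step 2, without any adjustment.** For 12 independent tests, 1 − 0.95^12 = 46%. With the three-arm structure and the assumed correlations it is 36%. False-discovery-rate control is therefore much better than nothing.

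**Step 3, why it still falls short.** BH compares the k-th smallest p-value with k × 0.05/12.
- If nothing is real, the smallest p-value faces 0.05/12 = 0.0042.
- If the six CFQ tests are all real and rejected, the smallest connectivity p-value faces 7 × 0.05/12 = 0.0292.
- Holm at the same point would ask for 0.05/(12 − 6) = 0.0083, which is 3.5 times stricter.
- For six independent null connectivity tests, 1 − (1 − 0.0292)^6 is about 16% under BH, and 1 − (1 − 0.0083)^6 is about 5% under Holm. Correlation lowers both.

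**Step 4, simulation.** Three arm means at 40 per arm, each contrast tested by z = difference / √(2/40), over all 12 tests:

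| True state | Null tests | Chance of any false primary claim, BH at 5% |
|---|---|---|
| Nothing real | 12 | 4.4–4.5% |
| CFQ: MBI 0.8 and physical training 0.4 above TAU; connectivity null | 6 | 7.6–7.8% |
| One contrast null, the other two 0.8, on one or both outcomes | 8 or 4 | 11.6–11.8% |
| CFQ effects very large; connectivity null | 6 | 12.8–12.9% |

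The ranges are the results of separate runs and, in the third row, of the variants. Holm stays at or below about 4% in every row.

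**Step 5, the other reading.** If each primary outcome gets a single time-by-condition test, there are two tests. BH then compares the larger p-value with 0.05 and the smaller with 0.025. That is Hochberg's procedure, which holds 5%.

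**The case against.** Three objections carry weight.

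**The family and the test order belong in an analysis plan.** This is a condensed article, and the family, the order and the primary visit are commonly fixed elsewhere. That is right, and their absence is not the point. The point is the rule the article does state. A separate plan could shrink the family, but while false discovery rate remains the rule for several primary contrasts, the family-wise error is not bounded at 5%.

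**Twelve tests is an interpretation.** This also stands. The multilevel model could yield one interaction test per primary outcome, and the problem then disappears (Step 5). However, H1 and H2 are pairwise and directional, and an omnibus test alone confirms neither.

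**Below 10% is not alarming.** At CFQ effects of 0.8 and 0.4 SD the figure is about 8%, and with nothing real it is under 5%. A reader might infer that the error exceeds 10% as a matter of course. The calculation does not support that: it passes 10% only in some configurations.

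Two further inferences also go too far. A reader might take the rule to pool the primaries with all secondary results, since the article labels the N-back analyses "confirmatory tests for H1 and H2, exploratory test for H3" while listing N-back activity as secondary. With 40 assumed secondary tests and all primaries null, the error would then run from about 1% to 24%, depending on how many secondaries are real. But the article does not define the family, and the rule directly follows the sentence on the intervention model.

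A reader might also infer that 40 per arm cannot show both H1 and H2. The article states no power and gives no effect for physical training, so any such figure rests on an invented position of that arm. The sample-size rationale also cites an earlier study of MBI and cognitive impairment after cancer treatment, beyond the small imaging studies.

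**Conclusion.** The concern holds in conditional form. The stated rule does not hold the chance of any false primary claim at 5%. With 12 tests it ranges from about 4% when nothing is real to about 12–13% in the less favourable configurations examined. It is about 8% with graded CFQ effects and null connectivity.

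These figures rest on the 12-test reading, BH at 5%, the two assumed correlations and the chosen effect sizes. None of these is given in the article. What does not depend on them is the property of the method: once some primary hypotheses are truly non-null, false-discovery-rate control over several contrasts gives weaker protection to the rest. No conclusion about the adequacy of the sample size follows.

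**What to change.** Name one primary visit and treat the other as secondary. The primary family is then 2 outcomes × 3 contrasts = 6 tests. Control the family-wise error over it at two-sided 5%, by either of these:
- Holm over the six contrasts.
- Alpha split between CFQ and connectivity, for example 2.5% each, with a fixed order of contrasts within each outcome.

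Restrict false-discovery-rate control to the secondary outcomes.

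A single chain that reaches connectivity only after all three CFQ contrasts succeed is not advisable. With assumed CFQ effects of 0.8 and 0.4 SD it would reach that named primary only about 11% of the time.

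The change needs new wording and no extra patients. It should be made before the blinded statisticians see outcomes by arm. The cost is power per primary contrast. For illustration, take a true difference of 0.8 SD at 40 per arm, so z = 0.8/√(2/40) = 3.58:
- Unadjusted at 5%: Φ(3.58 − 1.96), about 95%.
- First in order at 2.5%: Φ(3.58 − 2.24), about 91%.
- Holm at its strictest step, 0.05/6 = 0.0083: Φ(3.58 − 2.64), about 83%, which is a lower bound because later steps are easier.

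Under a fixed order, later contrasts may also go formally untested.
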